## Abstract

Age-related macular degeneration (AMD) has a strong genetic basis, but environmental factors such as smoking and a healthy diet can decrease the genetic fate by up to 50%. Current guidelines for clinical management include recommendations for a healthy lifestyle and antioxidant supplementation. However, many ophthalmologists do not inform their patients of this AMD-beneficial lifestyle. An important reason is the lack of trust that transition of lifestyle will be feasible in persons of advanced age and lack of methodology to measure lifestyle or its biological effects. To address these issues, we set up the lifestyle intervention study AMD-Life. It aims to investigate whether personalized risk-profiling (including genetic testing) and/or additional coaching can motivate patients to change their lifestyle. It also explores which biomarkers best reflect lifestyle change beneficial for AMD. The first year is a three-arm, self-contained open-label randomized clinical trial. A total of 150 AMD patients aged 55–85 years were randomized into three arms: (A) merely standard recommendations; (B) A conditions plus personalized risk profiling based on genetics and lifestyle, (C) B conditions plus coaching. The second year tests sustainability of lifestyle changes without active intervention. AMD-Life can provide further insight into the relevance of these interventions for the clinical management of AMD.

## 1. Introduction

Age-related macular degeneration (AMD) is a leading cause of blindness in the elderly of the Western world. Currently, more than 196 million people worldwide have AMD, and global aging will increase the number of affected persons to 288 million by the year 2040 [1,2]. The prevalence of early and intermediate AMD is ~20% in people aged over 65 years. These stages are characterized by the presence of yellow-white deposits (drusen) under the retinal pigment epithelium (RPE) and/or pigment changes, usually occurring without visual implications. The prevalence of the vision-disabling late AMD ranges from 3% in individuals aged 65 years to ~13% in those over 90 years [3]. This stage is characterized by either macular neovascularization (MNV, neovascular or wet AMD) or loss of RPE and photoreceptors (geographic atrophy, GA, or dry AMD) in the macular area. The transition from intermediate to the late stage of the disease occurs with a frequency of 3–6% per year [4]. Within 10 years, this will increase up to ~60%. The current therapeutic options for wet AMD are anti-VEGF injections, which improve vision drastically in the short term but often fail to protect against severe vision loss in the long term [5]. Therapy for GA has recently made progress with regimens controlling the complement pathway, but this still needs confirmation in real-world studies [6,7].

The genetic architecture of AMD has been mostly uncovered. Several years ago, a large genome-wide association study reported association with 52 common genetic variants in 34 loci [7]. The variants represented prominent pathways such as the complement cascade, lipid homeostasis, and extra-cellular matrix. A genetic risk score (GRS) that aggregated risks of these common variants showed a discriminative accuracy of 0.84 to correctly identify a person with late AMD [8]. In addition to common variants, many rare variants have been identified in genes involved in complements [9], collagen [10], coagulation pathways, and metalloproteinases [11]. Remarkably, although AMD is now one of the best genetically characterized complex diseases [7], genetic testing for AMD is still mostly a scientific enterprise and not a routine assessment in clinical practice. An important reason for this is the position of ophthalmic professional organizations, which do not advise genetic testing for AMD until treatment for specific disease-associated genotypes has been established.

Environmental factors also play a significant role in disease pathogenesis; in particular, smoking [12,13,14,15], dietary patterns [16,17,18], and physical activity [19] have been associated. We recently showed that persons in the most unfavorable tertile of these lifestyle variables had an increased risk of late AMD by at least two-fold [8]. Reduction of the risk is possible with nutrients that have antioxidative properties and polyunsaturated omega-3 fatty acids [16,20,21]. International dietary guidelines (United States, Canada, Germany, France, United Kingdom, The Netherlands, Japan, e.g.) recommend less meat and more plant-based dietary patterns including vegetables, fruit, whole grains, legumes, nuts and seeds, and (fatty) fish [22]. These recommendations are comparable with the Mediterranean diet pattern [23,24] and are also in line with the advice of the UN Food and Agriculture Organization and the World Health Organization [22,25]. However, data show that adherence to these recommendations is low [16,26,27]. In the Rotterdam Study, we recently investigated recommended minimum intake values (RMIV) of vegetables, fruit, and fish and the risk of AMD [16]. We found that only 4% of the participants consumed the recommended amounts of foods. However, those who did showed a significant decreased hazard ratio by more than half of incidence of advanced AMD. Two large clinical trials (AREDS 1; AREDS 2) provided evidence that supplementation with antioxidants and zinc can also significantly reduce disease progression [28,29]. Novel is the finding that intestinal microbiota [30] are associated with AMD, which may mediate the association with dietary factors [5,17,30], oral supplements [29], and other environmental factors [29].

Most preferred practice patterns for AMD recommend lifestyle measures, but the information provided to patients and adherence tend to be poor. Up to 60% of patients do not take oral supplements or use them incorrectly, and smoking cessation or long-term dietary changes are often not achieved [31,32,33,34]. One reason may be that retinal specialists do not convey the message adequately due to limited time, knowledge, or doubts about effectiveness [33,34,35,36,37]. This refutes the current view that healthcare professionals should play a significant role in motivating patients to change habitual patterns or behaviors that pose significant health risks. How does one motivate patients to take action and change behavior? A recent insight is that, at certain times, patients appear to be more receptive to behavioral change and lifestyle advice than usual [36,37], for example, when a disease has been diagnosed, they have received abnormal test results, or have been confronted with a high genetic risk. These are called ‘teachable moments’ and may be considered as optimal timing to start lifestyle counselling [36,37].

In the current AMD-Life trial, we aim to investigate which strategy is most successful in motivating patients to change the behavior that is driving them to vision loss: receiving only general information on risks and benefits, receiving detailed information about personalized risks and targets for change, or receiving coaching based on behavioral change technique (BCT) [38,39] and motivational interviewing (MI) [40,41]. We also aim to explore whether biomarkers in blood and the gut microbiome can be used to monitor lifestyle and lifestyle change, which can then be used to motivate patients further. This article provides the rationale and design of the study.

## 2. Materials and Methods

### 2.1. Study Design and Population

AMD-Life is a 2-year lifestyle intervention trial. The first year is a self-contained open-label randomized clinical trial with 3 intervention arms. The second year aims to investigate the sustainability of improved lifestyle without active intervention. Patients visit the research center 3 times: at baseline, month 12, and month 24. Ethical approval was obtained from the Medical Ethical Committee at Erasmus MC (MEC-2018-063). AMD-Life is registered at ClinicalTrials.gov (registration identifier: NCT05667441).

This study is designed as an inception phase study. We set up the main elements, test our assumptions and feasibility, check procedures, and focus on adherence, reporting participant and physician experience for the three different strategies tested, specifically targeting long-term behavior change.

Sample size calculation indicated that 50 eligible subjects per group would be sufficient to detect an effect size of 0.25 for adherence to lifestyle recommendations after the 12-month intervention (alpha: 0.05, power: (1-beta err prob.): 0.8897, calculated by G*Power).

Recruitment for the study started 2 August 2021 and is expected to end 1 July 2023. Participants are made aware of the study by their attending physician at outpatient clinics (OPC) of Erasmus MC Rotterdam, the Rotterdam Eye Hospital, Radboudumc, in Nijmegen, and other hospitals in the Netherlands. Interested candidates can apply online through the website: www.maculadegeneratie.nl (accessed on January 2023) with the apply button for participation, or by email or telephone.

Inclusion criteria: age between 55 years and 85 years, a diagnosis of intermediate AMD or unilateral late AMD, as determined by multimodal imaging and approved by the EyeNED Reading Center.

Exclusion criteria: participation in other intervention studies for AMD; living in retirement homes (because of difficulty in implementation of diet); dementia; macular pathology other than AMD; liver and kidney insufficiency; persons who are illiterate and have no independent trusted person with them to explain the informed consent form.

Prior to the study, all potential participants are informed and asked to provide written consent. Subsequently, participants are invited to visit the research center. Eligible participants are randomly assigned using a block-wise randomization procedure (in a 1:1:1 ratio) to one of three study arms. The assignment is by means of a computer-generated table with a random number sequence. This table gives a random order of allocation to the ‘Treatment Group’. The order is by date and time of the first study visit and stratified by gender and age categories (55–64, 65–74, 75–85). The first 125 participants are randomized per block (sets) of 6, and the remaining 25 per sets of 3. The researchers are blinded for randomization.

### 2.2. Interventions

The AMD-Life study tests three study arms, which each represent a different strategy to stimulate and increase adherence to a healthy lifestyle: (A) patients receive standard recommendations and supplements free of charge; (B) as in A, but patients additionally receive personal risk profiling based on phenotype as well as genetic and environmental risk factors; (C) as in B, but patients additionally receive professional coaching. The schematic overview of inclusion, exclusion, the three arms, and the follow-up is shown in Figure 1.

#### 2.2.1. Group A

Standard recommendations plus AREDS 2 and Omega 3 supplementation (‘standard care’)—n = 50. At the baseline visit, an experienced trial nurse informs the participant of personal outcomes of the measurements performed at the research center and of the standard AMD lifestyle recommendations. Participants also receive this information in a letter. The recommendations include refrain from smoking, perform regular physical exercise, strive for BMI < 25, and increase the intake of the dietary food groups of (green leafy) vegetables, fruit, (fatty) fish, and legumes. The Mediterranean Diet pattern is used as guidance for recommendations (for a more detailed description see Table 1). Participants receive oral supplements with antioxidants according to the AREDS 2 formula and Omega 3 forte fish oil free of charge (Table S1).

#### 2.2.2. Group B

Standard care plus personalized risk profiling—n = 50. Participants receive a personalized risk profile for motivational purposes. They are informed about their AMD genetic risk (low, medium, high, very high) based on the GRS, risk of progression, and the potential gain from lifestyle improvement. The four lifestyle factors of smoking, BMI, diet, and physical exercise are graded using a 13-point easy-to-use lifestyle scoring form (Figure S1 - page 1); participants receive their personal grades and can check their room for improvement.

#### 2.2.3. Group C

Standard care plus personal risk profiling plus coaching—n = 50. Participants receive coaching based on MI and the stages of BCTs using the AMD-Life coaching model (Figure 2): determination of awareness, motivation, perseverance and discipline, and goal setting. Depending on the stage and/or need of the participant, several tools, information leaflets, documents with assignments, and tables (e.g., specific foods and levels/concentrations of beneficial AMD-nutrients) are provided to the participant to enhance awareness and stimulate habitual change. Coaching sessions take place online by a 15–20 min videoconference twice a month for the first 2 months, followed by once a month for the following 10 months.

After an intervention of 12 months, all study participants visit the research center, after which the participants form a single group to observe the sustainability of lifestyle improvements. At this point, Group A receives insights into their lifestyle changes over the first year and is informed about their genetic risk, similarly to groups B and C, who received this information at month 0 (Figures S1 and S2). At month 24, the study ends with a third visit to the research center.

### 2.3. Avoiding Attrition Bias

Multiple strategies are employed to reduce attrition in all three arms, including an effective recruitment process, brief and informative encounters with staff members, a good tracking system to facilitate participant contact, anti-oxidant and fish oil supplementation free of charge, and the development of a trusting and collaborative relationship between researchers and participants.

If a participant wishes to withdraw from the study intervention, a telephone call is made prior to withdrawal to discuss the reason and possible solutions. If there is no solution, the reason for withdrawal is documented in the participant records for the subsequent analysis and the interpretation of the results.

### 2.4. Data Collection and Measurement

Data collection is performed at month (mo.) 0, 3, 6, 9, 12, and 24. Outcome variables, data collection, measurements, and time points are depicted in Figure 3.

#### 2.4.1. Ophthalmologic Examination

At mos. 0, 12, and 24, participants undergo a comprehensive ophthalmologic examination consisting of measurement of best-corrected visual acuity (VA); refractive error (TopCon TRK-2P objective refractometer); Macular Pigment Optical Density (MPOD; MPS II); intra-ocular pressure (IOP; non-contact tonometer); fundus photography, OCT, and OCTA (3D macula, 3D optic disk, wide, and angiography with T Topcon Triton plus, Topcon 3D OCT 2000-plus; Topcon TRC 50EX with a NIKON D7100 camera).

Features and stages of AMD are classified by grading of multimodal images according to a modification of WARMGS (CFP) [42] and IN-OCT (OCT) consensus by 4 experienced human graders. Quantification of lesions are determined using Deep Learning algorithms developed and available at EyeNED Reading Center [42,43,44,45].

#### 2.4.2. Genetic Factors

Subjects provide a saliva sample for DNA analysis 1 month prior to visiting the research center. Genotyping is performed for known common AMD risk variants, rare variants associated with AMD, and mutations in AMD-mimicking genes. The genotyping platform used is the Illumina Global Screening version 3 MD array with a custom content containing >3500 probes for detecting rare variants and mutations (GSAv3MD-GOALLv1) in CFH (n = 198), CFI (n = 90), C3 (n = 71), C9 (n = 20), ABCA4 (n = 1239), TIMP3 (n = 9), PRPH2 (n = 71), BEST1 (n = 27), CTNNA1 (n = 37), and MFRP (n = 2). Total genetic risk score (GRS) for common variants is calculated by the following formula for GRS, where Gi represents the genotype of variant i and βi represents the effect size of variant i (natural logarithm of the fully conditioned odds ratio of the minor allele of variant i), based on the GWAS of the International Age-Related Macular Degeneration Genomics Consortium [7]. Genotypes were coded as 0, 1, or 2 or, if the genotype is available from imputation, based on the number of minor alleles. Detailed information on SNPs used in GRS calculation is available at (Table S2). GRS is subsequently stratified into tertiles based on the distribution of GRS in the EYE-RISK cohort as Low (GRS < −0.057), Intermediate (GRS > −0.057 & < 1.131), or High (GRS > 1.1131) genetic risk [8]. High GRS is then stratified in equal proportion into High and Very High (GRS ≥ 3).

#### 2.4.3. Covariates

All questionnaires used in the AMD-Life study are digital/online. The participants receive an e-mail with a secure link to the online questionnaires, and data are entered directly into the AMD-Life database.

##### Social Demographics

We ask about baseline social demographic factors by means of a short questionnaire at mo. 0. This includes gender, age, education, eye disorders, family history of AMD, occupation, presence of comorbidity (such as diabetes, cardiovascular disease, hypertension), and living area (6-digit postal code).

##### Anthropometric Data

Anthropometric data are measured and collected at the research center at mos. 0, 12, and 24. Body measurements, including height, weight, and waist and hip circumference, are measured in kilograms and centimeters. Weight and height are used to estimate the body mass index (BMI = weight/(height)2). Blood pressure, systolic and diastolic, are measured, using an automatic sphygmomanometer. Hypertension is defined as a systolic blood pressure ≥ 140 mmHg or a diastolic blood pressure ≥ 90 mmHg. 

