##### Collecting Feces

To measure diversity and composition (i.e., alpha and beta diversity and single taxa) of the fecal microbiome over time, we ask participants to collect a sample of their feces at home at three time points: mos. 0, 12, and 24. Participants receive a feces collection kit with all necessary materials. The sample is collected using a preservative and stored at –80 °C upon arrival at the research center for later analysis. Medication use (such as antibiotics) is registered as well (yes/no; if yes, which).

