#### Other Study Parameters

Other study parameters are as follows: age, gender, blood pressure, hypertension, education and socioeconomic factors, comorbidity such as cardiovascular disease, medication, genetic susceptibility of AMD evaluated by GRS, major risk and protective variants, and rare variants.

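### Hypertension is defined by the visit reading alone, so participants whose diagnosed hypertension is controlled by medication are coded as not hypertensive

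*Protocol article*

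**What the plan says.** Four places in the protocol article bear on the point.

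- **Section 2.4.3, Anthropometric Data**, gives the definition: "Hypertension is defined as a systolic blood pressure ≥ 140 mmHg or a diastolic blood pressure ≥ 90 mmHg". The readings behind it are described just before: "Blood pressure, systolic and diastolic, are measured, using an automatic sphygmomanometer". Their timing is that of the section as a whole: "Anthropometric data are measured and collected at the research center at mos. 0, 12, and 24".
- **Section 2.4.3, Social Demographics**, describes a short questionnaire at month 0 that includes "presence of comorbidity (such as diabetes, cardiovascular disease, hypertension".
- **Section 2.4.4, Collecting Feces**, says "Medication use (such as antibiotics) is registered as well (yes/no; if yes, which".
- **Section 3.2, Other Study Parameters**, lists "age, gender, blood pressure, hypertension, education and socioeconomic factors, comorbidity such as cardiovascular disease, medication".

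The article does not say how the measured and the reported hypertension are to be combined, or which of them an analysis will use.

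**The concern.** A threshold on the visit reading identifies people whose pressure is high on that day. It does not identify people who have hypertension, because successful treatment moves the reading below the threshold and leaves the diagnosis in place. Eligible participants are "age between 55 years and 85 years", so some treated hypertension is to be expected, although the article gives no rate.

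Under the written rule the variable called hypertension is a dichotomised form of the blood pressure already listed beside it, and so adds no information to that measurement. The information that would make it a separate variable, diagnosis and treatment, is left out of the definition.

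Two uses are at stake. One is the description of the three arms at baseline. The other is any exploratory analysis, for instance of biomarkers against lifestyle or AMD features, that adjusts for hypertension. Such analyses are not protected by randomisation, and a covariate that places treated hypertensives among the unaffected would adjust incompletely.

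**Working it through.** **1. Is there a stated figure to reproduce?** There is none for hypertension. The only design calculation is the power statement in section 2.1 ("50 eligible subjects per group would be sufficient to detect an effect size of 0.25", alpha 0.05, power 0.8897). It can be reproduced as the between-groups test of a repeated-measures ANOVA with 3 groups, N = 150 and f = 0.25, if one assumes 2 measurements with correlation 0.5 (neither is stated). Then lambda = f² × N × m / (1 + (m − 1) × rho) = 0.0625 × 150 × 2 / 1.5 = 12.5. With 2 and 147 degrees of freedom this gives power 0.8898, against 0.8897 stated. Hypertension does not enter the calculation, so the power does not depend on this point.

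**2. What the rule does, case by case.** The readings are illustrative.

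| Participant | Reading (mmHg) | Code under the written rule | Other information on the same person |
|---|---|---|---|
| Diagnosed, treated, controlled | 130/78 | no | diagnosis reported at month 0; medication, if recorded |
| Diagnosed, reading above a limit | e.g. 150/85 | yes | agrees |
| No diagnosis, untreated, high on the day | e.g. 141/80 | yes | no diagnosis, no medication |
| No diagnosis, reading below both limits | e.g. 125/75 | no | agrees |

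The first row follows from the wording and needs no assumption. The third row can differ in the opposite direction.

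**3. How many?** Let p be the share of participants with diagnosed hypertension, t the share of those who are treated, and c the share of the treated who read below both limits. Suppose that all other diagnosed participants read above a limit. Then

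- number missed = 150 × p × t × c
- sensitivity of the rule for diagnosed hypertension = 1 − t × c

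The article gives none of p, t or c. With assumed values:

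| p | t | c | Missed of 150 | Sensitivity |
|---|---|---|---|---|
| 0.4 | 0.5 | 0.3 | 150 × 0.06 = 9 | 1 − 0.15 = 0.85 |
| 0.6 | 0.7 | 0.5 | 150 × 0.21 = 31.5 | 1 − 0.35 = 0.65 |
| 0.7 | 0.9 | 0.7 | 150 × 0.441 = 66.2 | 1 − 0.63 = 0.37 |

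Another way to set the inputs is to assume that 30–60% of all 150 are treated and 40–60% of those are controlled. That gives 150 × 0.3 × 0.4 = 18 to 150 × 0.6 × 0.6 = 54. The spread shows that the count comes from the inputs chosen and not from the article.

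**4. Which way does prevalence err?** Let e be the share of participants without a diagnosis who read above a limit at the visit. The coded prevalence minus p is (1 − p) × e − p × t × c, so the two errors cancel when e = p × t × c / (1 − p). In the first scenario this is 0.06 / 0.6 = 0.10; in the second it is 0.21 / 0.4 = 0.525. In the third it is 0.441 / 0.3 = 1.47, which no share can reach, so there the coded prevalence would be too low whatever e is. The sign therefore depends on four quantities that the article does not give.

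**5. Where is the variable used?** Hypertension is not an item of the 13-point lifestyle score (sections 2.4.5 and 3.1), not a secondary endpoint (3.2), and neither a stratification factor nor an eligibility criterion (2.1). Section 3.3 names only treatment group as an independent variable.

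**The case against.** The best reply is that a measured status and a reported diagnosis are different constructs. The article collects both, lists blood pressure, hypertension, comorbidity and medication separately, and nowhere says that the reading overrides the diagnosis. How raw items become an analysis covariate is commonly left to the analysis plan. This is a fair answer to the silence on combining the two. It does not answer the definition, which is stated in full, attached to the word hypertension, and placed under Covariates.

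The reply does rule out several stronger statements that a reader might infer:

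- **That the article contradicts itself.** It does not. The two variables can disagree for an individual, but nothing requires them to agree.
- **That baseline prevalence is understated.** That is certain only for treated, controlled participants. People without a diagnosis who read high on the day push the other way, and the net is unknown.
- **That the planned models carry residual confounding.** No stated model adjusts for hypertension. The discussion mentions a large set of covariates without naming this one.
- **That participants who start treatment will be counted as cured.** The reading is repeated at months 12 and 24, so the code could change, but no outcome or analysis of change in hypertension is stated.

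The reply is also right that the medication record is less certain than it looks. Its collection is described only within feces sampling, with antibiotics as the example, and antihypertensives are not named.

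**Conclusion.** The point holds as a flaw in the derivation of one listed covariate. Under the written rule, a participant with diagnosed hypertension controlled by medication is coded as not hypertensive, although the diagnosis is collected at month 0 and medication is listed among the parameters. That conclusion rests on the text alone.

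Its reach is limited to the baseline description and to any exploratory adjusted analysis that uses the variable. The primary comparison and the power are not affected. The counts of about 9 to 66 of 150 are illustrations that rest wholly on assumed shares. Neither the true number nor the net direction of the prevalence error can be derived from the article. The point is minor, but cheap to correct.

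**What to change.** For the analysis variable, code hypertension as present if any of these holds: an elevated reading by the thresholds already stated; hypertension reported in the month 0 questionnaire; or recorded use of antihypertensive medication, where the medication record allows it. Keep systolic and diastolic pressure as continuous variables, and label the reading-only variable *elevated blood pressure at visit*. Before relying on the third term, confirm that the medication record covers all drugs and not only those relevant to the feces sample; if it does not, the first two terms still apply.

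The cost is one line in the variable derivation and a label. The first two terms need no new data and place no burden on participants. There are two downsides. Part of the definition will rest on self-report, and some blood-pressure-lowering drugs are taken for other cardiovascular indications, so the medication term can code a person as hypertensive who is not.
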